### **7.2.1 Additional consent provisions for collection and use of participant data and biological specimens in ancillary studies, if applicable**

Potential participants will be asked to consent to receive invitations for ethically approved ancillary studies.

### **7.2.2 Participant safety**

After randomisation, the participant's GP will be informed of their participation in the study. When informed of their patient's participation in the trial, GPs will be advised to manage their patient for exacerbations as per normal clinical practice and that they are to assume the participant is taking bisoprolol and the prescription of interacting drugs should be avoided.

During a face-to-face consent visit, participants will be given (and advised to carry) a credit card sized alert card giving brief information about the trial and advice for clinicians, contact details for the local investigator, and the contact details for emergency unblinding. If patients are recruited into the study without a face-to-face recruitment visit, the alert card will be sent to them after randomisation.

If the participant has nominated a "best contact", the best contact will be contacted by post to confirm their willingness to act as such. Best contact information is collected in case it is not possible to contact the participant themselves – for example if they have moved house or are in hospital.

## **7.3 Randomisation**

A computerised randomisation system created by CHaRT will allocate participants with equal probability to intervention or control arms, stratified by centre (secondary care site, primary care area), and where participants were identified (primary care, secondary care). This randomisation application will be available 24 hours a day, 7 days a week as an interactive internet based application. Randomisation should only be carried

out once the eligibility has been confirmed by a medical doctor listed on the delegation log, and following consent. The randomisation application will be available to people listed on the delegation log with that responsibility and is not restricted to those who confirm eligibility or take consent.

Participants will be randomised to bisoprolol or placebo. Bisoprolol will be in the form of 1.25mg tablets. Each bottle will contain 168 tablets. The first bottle of study medication (or placebo) will be provided to the participant via the Central Clinical Trials Pharmacy. This first bottle of study medication will be delivered to participants via a courier service (or other signed for delivery service) operated by a third party.

### **7.3.1 Method of implementing the randomisation/allocation sequence**

The random allocation sequence will be generated using permuted blocks. This will provide randomly generated blocks of entries of varying sizes permuted for each combination of region and recruitment setting (primary or secondary care).

Each entry will be assigned a treatment according to a randomly generated sequence utilising block sizes of 2 or 4. Each treatment option will be assigned an equal number of times within each block, ensuring that the total entries assigned to each treatment remained balanced. The sequence of blocks will be random, so it will not be possible to determine the next treatment to be allocated based on previous allocations made during the randomisation process. The random permuted blocks that define how treatments will be allocated to participants will be created by the CHaRT Programming team during the system development process. The system built to utilise these permuted blocks will be tested by a run of simulated randomisations that allow the outcomes to be cross-checked and validated. Before the randomisation system goes live, enough blocks will be created to ensure entries exist for the maximum expected number of participants across the maximum expected number of centres. However, the randomisation system is flexible enough to allow the option to add further permuted blocks to the list if more are required during the lifetime of the trial. In such circumstances, randomly generated sequences in blocks of 2 and 4 continue to be utilised.

### **7.4 Blinding**

To ensure double blinding, study medication/placebo will be identical in terms of appearance, taste, touch and smell and dispensed in numbered containers of identical appearance and labelling. Labelling for both study medication and placebo will have the same batch number and expiry date.

### **7.5 Emergency unblinding**

This section of the protocol has been written to be in line with the Sponsor SOP (NHSG/UoA SOP-QA-35 - Unblinding). The decision to unblind a single case should be made when knowledge of an individual's allocated treatment is required:

- to enable treatment of severe adverse event/s, or
- in the event of an overdose
- to enable reporting of a SUSAR

Where possible, requests for emergency or unplanned unblinding of individuals should be made via the Trial Manager based in CHaRT at the University of Aberdeen. Agreement of the Chief Investigator or a delegate will then be sought. However, in circumstances where there is insufficient time to make this request or for agreement to be sought, the treating clinician should make the decision to unblind immediately. Out of hours requests will be made through the BICS on-call consultant (via BICS mobile number). This contact number will be on the emergency card that participants are given to carry (section 7.2.2).

In addition, details of how a patient can be unblinded will be included in the site file and in the patient's medical records.

Unblinding will be done via the IVRS (telephone or web-based application). In the event of failure of the IVRS (for example if the server is down), unblinding will be conducted by the on-call pharmacist based at Aberdeen Royal Infirmary who can be obtained by the switchboard ([name]).

All instances of unblinding should be recorded and reported in writing to CHaRT by the local investigator, including the identity of all recipients of the unblinding information. CHaRT will inform the sponsor of all unblindings.

Allocation should not routinely be revealed to CHaRT personnel, the Chief Investigator, or members of the research team at the site. In the event of unblinding to report a SUSAR. The Chief Investigator and a member of the trial office team will take responsibility for unblinding and reporting.

The Data Monitoring Committee have the right to receive reports of all serious adverse events (in real time) with associated unblinding information. The Sponsor has agreed that these unblinding requests do not need individual approval from the Sponsor and therefore Sponsor and CI approval is not required to unblind these cases provided the agreed process is followed. A member of the CHaRT programming team will unblind the cases and provide the allocation to the Data Monitoring Committee. The allocation will not be revealed to the Chief Investigator, the trial office team, or members of the research team at the site.

At the end of the 12-month follow-up period, participants (or their GPs) may request to be unblinded in order to inform ongoing treatment decisions. In such cases, the CI will have a telephone conversation with the participant or GP, to include discussion of the methodological and scientific advantages of maintaining the blind until the data is analysed. If the CI is not available to have this conversation, it will be made by another senior member of the trial team. Following this conversation, if the participant or GP still wishes to be unblinded, a request to Sponsor to permit unblinding will be made. If the Sponsor agrees, the unblinding will be done by a member of the CHaRT programming team such that the CI, trial office team and site research team can remain blind to treatment allocation.

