## 7.6 Trial assessments

After obtaining written informed consent, participants will be assessed as follows:

- At the recruitment visit; face to face or via telephone/video call
- At 1 week, face to face\* (dose titration)
- At 2 weeks, face to face\* (dose titration)
- At 3 weeks, face to face\* (dose titration)
- At 4 weeks, face to face\* (dose titration)
- At 6 months (26 weeks); face to face\*
- At 12 months (52 weeks); face to face\*
- 1 week after cessation of study medication by telephone
- Post study; examination of hospital and GP records to obtain primary outcome data.

\* Whilst the COVID-19 pandemic is ongoing, the recruitment visit can be done as face-to-face, with appropriate precautions in place (PPE, social distancing, hand hygiene etc). All other visits (titration, and 6/12 month follow-up) will be conducted remotely, via telephone/video call. Following a remote assessment, if there are clinical concerns, the site can arrange a face-to-face visit with appropriate precautions in place.

In the event that a participant is unable to complete a scheduled assessment because of an acute illness e.g. exacerbation of COPD, the assessment will be appropriately postponed, to be conducted when the participant is stable, ideally within 4 weeks of the scheduled assessment. Similarly, participants who are unable to attend a scheduled assessment for another reason will have this rearranged, ideally within 4 weeks of the scheduled assessment. Participants unable to attend for face to face assessment at six and twelve months can be

followed up by telephone, a home visit, or sent the questionnaire to complete at home. Similarly, recruitment of patients who, for example have limited mobility or who live some distance from the study site, can be carried out during a home visit. During the COVID-19 pandemic, to reduce footfall in hospitals and GP practices, a face-to-face recruitment visit can be done at home, with appropriate COVID-19 measures in place (PPE, social distancing, hand hygiene).

The schedule for data collection within the study is outlined in Table 2 (overleaf).

Potential participants will be informed in the PIL that they can raise any issues with the study team who will arrange further examination if indicated. If the participant or nurse have concerns, these will be discussed with a medically qualified local investigator and suitable arrangements made for the participant to be seen at a later date.

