### **7.12 End of trial**

The end of clinical follow-up for each participant is defined as completion of the follow-up visit at 12 months. The end of clinical follow-up is when the last participant completes their follow-up visit at 12 months. The end of the trial is defined as the end of funding (currently 31 January 2023; but this may be extended and if so, a further amendment to protocol will be made).

The Funder, Investigators and/or the Trial Steering Committee have the right at any time to terminate the study for clinical or administrative reasons.

The end of the trial will be reported to the REC and Regulatory Authority within 90 days, or 15 days if the study is terminated prematurely. The Investigators will inform participants and ensure that the appropriate follow up is arranged for all involved.

A summary report of the trial will be provided to the REC and Regulatory Authority within 1 year of the end of the trial. An end of trial report will also be issued to the funders at the end of funding.

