#### Post-trial access to IMP

At the end of the study we will inform the participants and their GPs of the results of the study and their allocation status. However, we do not plan to unblind individual participants at the end of their individual period of clinical follow-up (i.e. 12 months). Thus, participants will not be told whether they were taking bisoprolol at the end of their clinical follow up. Participants will be reminded that bisoprolol is not licensed for the treatment of COPD and we would not advise its use until its therapeutic role is established. However, if a participant wishes to take bisoprolol, the GP can be advised of this by letter. In the letter we will indicate to the GP that this would be outwith the licence for bisoprolol, that the patient may have been on placebo or bisoprolol and that dose-titration would be required.

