## 9.2 Operational definitions for (S)AEs

In this trial:

- SAEs will be recorded from the time a participant consents to join the study until the end of the weaning period after the 12 month follow-up (see notes in section 8.7.2). Participants who withdraw from taking the study drug during the 12 month follow-up period will have SAEs recorded from the time the participant consents to join the study until 28 days after ceasing study medication. Participants who never start taking the study drug will have SAEs recorded for 28 days from the time they consent to join the study. All adverse reactions will be recorded for the same period of time described above.
- Hospitalisations for treatment planned prior to randomisation and hospitalisation for elective treatment of a pre-existing condition will **not** be considered or recorded or reported as an SAE. Complications occurring during such hospitalisation will also not be considered, recorded or reported as an SAE – unless there is a possibility that the complication arose because of the study medication (i.e. a possible adverse reaction).
- Exacerbations of COPD or hospital admissions as a consequence of exacerbations of COPD will **not** be considered as AEs or SAEs because they are primary and secondary outcomes for the trial. These will be recorded as part of the trial outcomes, but will not be considered or recorded or reported as AEs or SAEs. Confirmed cases of pneumonia should be captured as SAEs.

All other SAEs (including SARs) should be reported to the trial office.

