### **13.11 Post trial care**

At the end of the study participants and their GPs will be informed of the results of the study and their allocation status. However, there are no plans to unblind individual participants at the end of their individual period of clinical follow-up (i.e. 12 months). Thus, participants will not be told whether they were taking bisoprolol at the end of their clinical follow up. Participants will be reminded that bisoprolol is not licensed for the treatment of COPD and we would not advise its use until its therapeutic role is established. However, if a participant wishes to take bisoprolol, the GP can be advised of this by letter. In the letter we will indicate to the GP that this would be outwith the licence for bisoprolol, that the patient may have been on placebo or bisoprolol and that dose-titration would be required.

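### On-request unblinding after 12 months (7.5) conflicts with 8.4 and 13.11, and its release is not held until the weaning-period safety data are in

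*Protocol*

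**What the plan says.** Section 7.5, after the emergency rules, adds a route that is not an emergency: "At the end of the 12-month follow-up period, participants (or their GPs) may request to be unblinded in order to inform ongoing treatment decisions". The chief investigator, or another senior member of the trial team, first talks to the requester about the value of keeping the blind. Then, "if the participant or GP still wishes to be unblinded, a request to Sponsor to permit unblinding will be made". If the Sponsor agrees, the programming team releases the allocation "such that the CI, trial office team and site research team can remain blind to treatment allocation".

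Section 8.4, under post-trial access to the drug, says: "Thus, participants will not be told whether they were taking bisoprolol at the end of their clinical follow up". Section 13.11 repeats this and adds that "there are no plans to unblind individual participants at the end of their individual period of clinical follow-up". Both offer a participant who wants bisoprolol afterwards a letter to the GP that leaves open which treatment was taken.

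Three other sections fix the timing:
- Section 7.12: "The end of clinical follow-up for each participant is defined as completion of the follow-up visit at 12 months".
- Section 9.2: SAEs are recorded "until the end of the weaning period after the 12 month follow-up", and adverse reactions over the same period.
- Section 8.7.2: adverse effects during weaning go into the case report form, and a telephone call follows one week after the drug is expected to stop.

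**The concern.** There are two defects.

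The first is a conflict between sections. A site or GP asked about treatment after month 12 finds a route to the allocation in 7.5 and a flat refusal in 8.4 and 13.11. Who is unblinded could then depend on which section was read.

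The second is timing. The request route opens when clinical follow-up ends, but blinded data collection has not ended. The participant is the person who reports symptoms during weaning, and is also the person who may learn the allocation. Section 8.7.2 gives possible rebound myocardial ischaemia as the reason for weaning, so this short period has a safety question of its own. Reports made with allocation known are harder to compare between arms, and they would come from participants who chose to ask.

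A narrower problem concerns staff. Section 7.1 allows a general practice to be an independent study site, and section 9.4 gives causality assessment to the principal investigator. If the GP who asks is on the site research team, that team is no longer blind for that participant.

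**Working it through.** No sample size, power or alpha figure is involved. The check sets the sections side by side and works out the open window.

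**1. Do the sections agree?**

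| Section | Position at 12 months | Cross-reference |
|---|---|---|
| 7.5 | Participant or GP may ask; released if the Sponsor agrees | none to 8.4 or 13.11 |
| 8.4 | No plan to unblind; participants will not be told | none to 7.5 |
| 13.11 | Same as 8.4 | none to 7.5 |

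The statement that no unblinding is planned can stand beside 7.5 as a default with an exception. The statement in 8.4 and 13.11 that participants will not be told cannot, because it admits no exception.

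**2. How long are safety data still open?** The inputs are the weaning table in 8.7.2 and the call times in 7.8. From the table, weeks on drug after the final visit = tablets − 1. From 7.8, week of the call = number of tablets.

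| Tablets a day | Weeks of weaning | Call at week |
|---|---|---|
| 1 | 1 − 1 = 0 | 1 |
| 2 | 2 − 1 = 1 | 2 |
| 3 | 3 − 1 = 2 | 3 |
| 4 | 4 − 1 = 3 | 4 |

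The last row reproduces the 3-week wean given in the synopsis. In every row the call falls one week after the drug stops, as 7.6 and 8.7.2 say. Adverse reaction and SAE recording therefore stays open for 0 to 3 weeks after the point that 7.12 calls the end of clinical follow-up, and the last contact comes 1 to 4 weeks after it. Section 7.5 contains no condition tied to either date.

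**3. Is the primary outcome exposed?** Section 3.3 makes it participant-reported, and 7.6 ascertains it at the 6- and 12-month assessments. The list in 7.6 also has the entry "Post study; examination of hospital and GP records to obtain primary outcome data" without restriction, and so does Table 2. The text of 7.6 on exacerbations directs the GP-record check to participants who neither attend at 12 months nor complete the questionnaire. Such a check concerns the treatment year, so the entries it reads would mostly predate any unblinding.

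One residual route exists. Section 7.6 lets the 12-month assessment be postponed, ideally by no more than 4 weeks, and 7.5 does not say whether its 12-month period ends by calendar or at the completed visit. On the calendar reading, a participant could be unblinded before giving the 12-month report. The definition in 7.12 points to the completed visit.

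**The case against.** The safeguards in 7.5 are substantial. It grants a request, not a right: there is a conversation intended to preserve the blind, the Sponsor may refuse, and the release bypasses the chief investigator, the trial office and the site team. Causality ratings therefore mostly remain in blinded hands. Sections 8.4 and 13.11 can be read as the default and 7.5 as its exception. Participants on one tablet have no weaning, and most of those who stopped early have no recording window left.

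Most of this stands, and it limits the size of the problem. It does not remove it. None of the safeguards requires weaning or the final call to be finished. They shield staff, whereas the symptoms are reported by the participant. Sponsor discretion could cover a GP who is on the site team, but the protocol gives no rule for that case. The default-and-exception reading fails on the unqualified wording in 8.4 and 13.11.

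A reader might infer something stronger: that participants are unblinded at the 12-month visit itself, and that the primary outcome is then collected with allocation known. The documents do not support this. Section 7.5 only accepts a request from that point. The primary outcome has by then been reported, except on the calendar reading described above, and the record check is aimed at participants who gave no 12-month report.

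**Conclusion.** The point holds in a limited form. Sections 7.5, 8.4 and 13.11 contradict each other on whether a participant can learn the allocation after month 12. Section 7.5 also places the request before the safety data close, by 0 to 3 weeks of weaning and by up to 4 weeks to the last call. Some participant-reported adverse reactions and SAEs could therefore be collected with allocation known, and a requesting GP on the site team would defeat the intended blinding of that team.

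The primary comparison is largely unaffected. The protocol gives no basis for estimating how many will ask, how many requests the Sponsor will grant or how quickly, so the number affected is unknown. With the approval steps and the short window it is probably small. The conclusion assumes that the 12-month period in 7.5 ends at the completed visit, as in 7.12. The change is still worth making, because the contradiction is plain and the correction is cheap.

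**What to change.** In 7.5, state that non-emergency unblinding on request is released only when that participant's 12-month assessment is completed and the post-weaning call and its adverse reaction and SAE data are entered. For a participant already off the drug, the matching condition is that any 28-day recording window under 9.2 has closed. Add that, where the requester is on the site research team, either a blinded colleague makes any remaining assessments for that participant or the allocation goes to a clinician outside the team.

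In 8.4 and 13.11, keep no individual unblinding as the default, describe the 7.5 route as its exception, and cross-refer. Emergency unblinding is unchanged.

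The cost is wording in three sections and a status check before release. The requester waits up to about 4 weeks longer. Release need not wait for the post-study record check, which has no stated date, nor be put off to the end of the trial for GPs on the site team. Either would be a much longer delay for little gain.

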## 7.6 Trial assessments

After obtaining written informed consent, participants will be assessed as follows:

- At the recruitment visit; face to face or via telephone/video call
- At 1 week, face to face\* (dose titration)
- At 2 weeks, face to face\* (dose titration)
- At 3 weeks, face to face\* (dose titration)
- At 4 weeks, face to face\* (dose titration)
- At 6 months (26 weeks); face to face\*
- At 12 months (52 weeks); face to face\*
- 1 week after cessation of study medication by telephone
- Post study; examination of hospital and GP records to obtain primary outcome data.

\* Whilst the COVID-19 pandemic is ongoing, the recruitment visit can be done as face-to-face, with appropriate precautions in place (PPE, social distancing, hand hygiene etc). All other visits (titration, and 6/12 month follow-up) will be conducted remotely, via telephone/video call. Following a remote assessment, if there are clinical concerns, the site can arrange a face-to-face visit with appropriate precautions in place.

In the event that a participant is unable to complete a scheduled assessment because of an acute illness e.g. exacerbation of COPD, the assessment will be appropriately postponed, to be conducted when the participant is stable, ideally within 4 weeks of the scheduled assessment. Similarly, participants who are unable to attend a scheduled assessment for another reason will have this rearranged, ideally within 4 weeks of the scheduled assessment. Participants unable to attend for face to face assessment at six and twelve months can be

followed up by telephone, a home visit, or sent the questionnaire to complete at home. Similarly, recruitment of patients who, for example have limited mobility or who live some distance from the study site, can be carried out during a home visit. During the COVID-19 pandemic, to reduce footfall in hospitals and GP practices, a face-to-face recruitment visit can be done at home, with appropriate COVID-19 measures in place (PPE, social distancing, hand hygiene).

The schedule for data collection within the study is outlined in Table 2 (overleaf).

Potential participants will be informed in the PIL that they can raise any issues with the study team who will arrange further examination if indicated. If the participant or nurse have concerns, these will be discussed with a medically qualified local investigator and suitable arrangements made for the participant to be seen at a later date.

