### **3.3 Primary endpoint/outcome**

The primary outcome measure will be the total number of exacerbations of COPD necessitating changes in management (minimum management change - use of oral corticosteroids and/or antibiotics) during the one year treatment period, as reported by the participant.

The primary economic outcome measure will be cost-per-QALY gained during the one year treatment period.

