#### *Health care utilisation*

Health care utilisation during the previous 6 months will be ascertained at recruitment and the 6 and 12 month assessments (see section 10.5).

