#### **10.5 Economic evaluation**

An NHS economic evaluation will be conducted in two stages. Firstly, the cost-effectiveness of treatment will be calculated for the within trial period based on observed data. Secondly, the results of the trial will be extrapolated to patient lifetimes using cost-effectiveness modelling.

The within trial analysis will make use of the health care resource use data (translated to a cost-per-patient using unit costs standard reference sources), the exacerbation rate associated with the treatment arms, and the quality of life effects estimated from the EQ-5D-5L combined with utility data to calculate QALYs. Non-parametric bootstrapping will be used to capture sampling uncertainty in the observed data and results will be presented as cost-per-exacerbation avoided and cost-per-QALY gained within the trial period with accompanying confidence intervals (or cost-effectiveness acceptability curves if more appropriate).

The extrapolation analysis will make use of regression estimates of exacerbation on cost and quality of life from the trial, as well as previously published models of COPD, to guide the extrapolation to patient lifetimes. In addition to sampling uncertainty, extensive sensitivity, analysis will be performed to understand the importance of alternative modelling assumptions for the extrapolated results.

*Collection of data:* Data collection from the trial will focus on estimating the use of primary or secondary NHS health care resources.

*Participant Costs:* Direct health care costs falling on the participant costs will not be included. It is not anticipated that these costs will be substantial and, in any case, fall outside of the health service reference case for this analysis.

*NHS Costs of Health Services Used:* Health care utilisation during the previous 6 months will be ascertained at recruitment and the 6 and 12 month assessments by a modified version of the Client Service Receipt Inventory (CSRI) [58]. The CSRI is a research questionnaire for retrospectively collecting cost-related information about participant's use of health and social care services.

*Cost Effectiveness:* Following a method previously used in large international trial for COPD treatments [59],

the within trial analysis will use regression techniques to simultaneously capture heterogeneity of cost-effectiveness among the patients studied, while adjusting for any missing data.

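### Visits postponed until the participant is stable, combined with a fixed six-month recall of health care use, give overlapping and missing cost windows and remove acute EQ-5D-5L losses

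*Protocol*

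**What the plan says.** Protocol section 7.6 schedules the main follow-up assessments as "At 6 months (26 weeks); face to face" and "At 12 months (52 weeks); face to face". If acute illness, with a COPD exacerbation as the example, means a participant cannot complete one, "the assessment will be appropriately postponed, to be conducted when the participant is stable, ideally within 4 weeks of the scheduled assessment". Visits missed for other reasons are rearranged with the same four-week aim. Four weeks is a target, not a limit. Participants who cannot attend face to face at 6 or 12 months can be "followed up by telephone, a home visit, or sent the questionnaire to complete at home", and during the pandemic all follow-up assessments are remote.

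The recall period for resource use does not move with the visit: "Health care utilisation during the previous 6 months will be ascertained at recruitment and the 6 and 12 month assessments". Section 10.5 repeats that period for the modified Client Service Receipt Inventory (CSRI). Nothing ties it to the date of the preceding assessment.

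EQ-5D-5L is collected at recruitment, 6 and 12 months only (section 7.6 and Table 2). Section 10.5 takes "the quality of life effects estimated from the EQ-5D-5L combined with utility data to calculate QALYs". Section 3.3 states: "The primary economic outcome measure will be cost-per-QALY gained during the one year treatment period".

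**The concern.** A look-back of fixed length covers the treatment year exactly once only if both visits fall on their due dates. The protocol allows them to move, and names exacerbation, the event that defines the primary clinical outcome, as a reason. When the 6-month visit slips for that reason, the period counted twice follows an exacerbation, and the period lost is the start of treatment, during titration.

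The same rule affects utilities. Two of the three EQ-5D-5L readings can move from an acute state to a recovered one, and never the reverse. Sparse sampling alone adds noise. Sampling that avoids the ill state loses utility decrement in one direction, and loses more in the arm with more exacerbations. Both components of the primary economic outcome are therefore linked to exacerbation through the timing rule.

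**Working it through.** **Starting figures.** The protocol gives no figure for either effect. The exacerbation rates come from section 10.1: 2.22 per year (SD 1.86) on placebo and 1.89 on bisoprolol. They reproduce the plan's sample size: n = 2 × (1.960 + 1.282)² × 1.86² / 0.33² = 668 per arm by the normal approximation, and 669 with the t distribution; 669 / 0.85 = 787.

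**Recall windows.** Let the visits be d6 and d12 weeks late, with six months taken as 26 weeks. The windows are d6 to 26 + d6, and 26 + d12 to 52 + d12. Overlap = max(0, d6 − d12). The gap at the start is d6. The gap in the middle is max(0, d12 − d6). Recall beyond week 52 is d12.

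| 6-month visit (week) | 12-month visit (week) | Windows (weeks) | Counted twice | Never asked | Beyond week 52 |
|---|---|---|---|---|---|
| 26 | 52 | 0–26, 26–52 | 0 | 0 | 0 |
| 28 | 52 | 2–28, 26–52 | 2 | 2 (start) | 0 |
| 30 | 52 | 4–30, 26–52 | 4 | 4 (start) | 0 |
| 30 | 54 | 4–30, 28–54 | 2 | 4 (start) | 2 |
| 30 | 56 | 4–30, 30–56 | 0 | 4 (start) | 4 |
| 26 | 56 | 0–26, 30–56 | 0 | 4 (weeks 26–30) | 4 |

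Total recalled time is always 26 + 26 weeks.

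**Size of the cost effect.** Assumptions not in the protocol: episodes last D = 1, 2 or 4 weeks; every participant ill at week 26 is postponed to recovery (at most four weeks); the 12-month visit is on time.

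- Placebo episodes in progress at week 26: 2.22 × D/52 = 0.043, 0.085 or 0.171 per participant. Some participants have more than one, so about 4%, 8% or 15% of placebo participants would be delayed, against about 4%, 7% or 13% on bisoprolol.
- An episode that prevents the week-26 visit has normally begun by week 26, so only its use from week 26 onward falls in both windows. If its costs arise at onset, the duplicated share is 0%. If they are spread evenly over the episode, it is about 50%.
- Inflation of recorded exacerbation costs is therefore between 0 and 0.5 × D/52, that is 0 to 1.0%, 1.9% or 3.8%. The factor is the same in both arms, so the between-arm difference inflates by the same percentage.
- A simulation with gamma-Poisson counts at these rates, with dispersion taken from the SD of 1.86, agrees: 0% with onset costs, and about 1%, 2% and 4% with spread costs.

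**Size of the QALY effect.** The true acute between-arm difference is (2.22 − 1.89) × D/52 × u, with u an assumed acute utility loss of 0.1 to 0.3.

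- Lowest: 0.33 × 1/52 × 0.1 = 0.0006.
- Middle: 0.33 × 2/52 × 0.2 = 0.0025.
- Highest: 0.33 × 4/52 × 0.3 = 0.0076.

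With linear area under the curve, the three readings carry weights 0.25, 0.50 and 0.25. On-schedule follow-up readings would capture 0.50 + 0.25 = 75% of this on average, or 0.0019 in the middle case. Readings always taken when stable capture about zero.

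**Against sampling error.** The protocol gives no SD for QALYs. With 787 per arm, the standard error of the difference is SD × √(2/787) = 0.0504 × SD. The middle value of 0.0025 is below one standard error unless the SD is under about 0.05, and the highest, 0.0076, unless it is under about 0.15.

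**The case against.** Postponement applies only to participants who cannot complete the assessment. Telephone, home or postal follow-up is allowed, and many exacerbations treated in primary care would not prevent a telephone call. This stands, and makes the sizes above upper limits for the share postponed. It does not remove the point: the remote routes are offered to those who cannot attend face to face, whereas the specific rule for acute illness is postponement.

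Duplicates could be removed in analysis. Separating exacerbations by two weeks and analysing time to first exacerbation both need dated episodes, and admissions are also collected separately. An analysis plan or the modified CSRI, neither shown, may deal with the overlap. That stands for dated events. No analysis can recover contacts in weeks nobody asked about, or an EQ-5D-5L reading never taken during illness.

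Three EQ-5D-5L time points miss most individual episodes whatever the visit rule, and stable readings can still show lasting effects of exacerbations. Both are true. What postponement adds is that the loss runs one way. The four-week stability rule at entry applies equally to both arms and adds no between-arm bias.

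A reader might infer that the delaying exacerbation is costed twice in full. The documents do not support that: use before week 26 falls in the first window only, and nothing is duplicated if the 12-month visit is equally late. A reader might also infer that the lifetime model simply inherits an attenuated utility effect. Section 10.5 draws on published COPD models as well as the trial regressions, and plans extensive sensitivity analysis.

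**Conclusion.** The point holds as a defect of data collection, and it merits a cheap improvement. As written, the recall rule produces overlapping and unrecalled periods whenever the 6-month visit is later than the 12-month visit relative to schedule, and the postponement rule ties some of these delays to exacerbations. The distortion of exacerbation costs is about 0 to 4%, and 0 to 2% for two-week episodes, if every ill participant is postponed. The acute between-arm utility difference exposed to loss is about 0.001 to 0.008 QALY, probably below sampling error. Episode duration, utility loss and the timing of costs within an episode are assumptions.

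It would be tempting to conclude that cost-per-QALY is biased in a known direction. That is not established. If bisoprolol works, duplicated costs slightly overstate its savings while stable-state readings understate its QALY gain. These push the ratio in opposite directions, and nothing makes them cancel.

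**What to change.** 1. At 6 and 12 months, ask for health care use since the last completed assessment, or since randomisation if there was none, up to week 52, with the start date pre-filled. A late 6-month visit then produces neither overlap nor gap.
2. Collect EQ-5D-5L at its due date by telephone or post whenever the participant can answer, even if the rest of the assessment is postponed. Record the actual completion date and whether an exacerbation is ongoing, and use actual dates in the QALY calculation.
3. Add one within-trial QALY sensitivity analysis that applies a utility decrement per exacerbation.

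The cost is a change of questionnaire wording, wider use of follow-up routes that section 7.6 already allows for those unable to attend face to face, and one extra analysis. Some unwell participants will be contacted and may decline, and recall becomes longer for those who miss the 6-month visit.
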